#### Primary outcome

Informed choice will be evaluated based on the following primary outcomes: consistency of knowledge about CRC screening, attitudes towards CRC screening, and screening uptake [34].

Knowledge will be measured via questionnaire before and after intervention using a seven-item scale developed by the authors based on both a literature search and patient information needs as previously clarified in focus group interviews [25]. Post-intervention levels and changes from baseline to follow-up will be evaluated.

Screening attitudes will be estimated using the translated four-item attitudes scale, ranging from 4 to 28 points [34]. The scale has been translated into Danish from English with conventional forward-backward translation [35]. Attitudes will be assessed at baseline and at follow-up.

Data on screening uptake will be collected from the CRC screening program database. Citizens will be defined as having taken up CRC screening if they return a stool sample within three months (90 days) after the screening invitation has been sent out [36].

#### Secondary outcomes

The 16-item decisional conflict scale [37] will be used to measure decisional conflict, i.e. uncertainty about making the right choice. It comprises five subscales, including the decisional support subscale and the (perceived) effectiveness of the decision subscale. Scores range from 0 to 100 and data are collected at follow-up.

Worry about CRC will be assessed using three items on worry about CRC. Two items assess worry and anxiety when considering CRC screening and one assesses worry about the result of a screening test. Items have also been developed by the authors based on literature searches [19, 20, 38–40]. Scores are in the range of 3–15. Assessments are made at baseline and follow-up.

Health literacy is a multidimensional measure of a person’s ability to access, understand, appraise, and apply information about healthcare, disease prevention, and health promotion [41]. It will be measured at baseline using the 16-item HLS-EU-Q16 scale [41].

The use of the decision aid will be measured among citizens receiving an invitation to use it. However, detailed process data will not be collected, since the primary aim of this trial is to investigate the effectiveness of having the decision aid provided, regardless of actually reading it. Usability and acceptability have been further assessed in the development phase of the decision aid [26].

#### Background data

Background data on participants’ sociodemographic and socioeconomic characteristics will be obtained from Statistics Denmark [42] by the end of the study period. These data are updated annually.

Lower educational attainment is defined according to the UNESCO classification of basic education as < 10 years of education [43].

Family income will be divided into three categories based on lower, middle, and upper tertiles of the dataset. Occupation is a categorical variable with the following six categories: Employed; Self-employed/chief executive; Unemployed/receiving benefits; Retired; Social welfare recipients; and Others. Marital status is dichotomized into two categories: married/cohabitant and single. Ethnicity will be a categorical variable with three categories: Danish; Western immigrant (Western Europe and North America); and non-Western immigrant (Table 1).

#### Questionnaires

Three different questionnaires will be administered in this trial: the baseline (knowledge, seven items; attitudes, four items [34]; worry, three items; health literacy – HLS-EU-Q16, 16 items [41, 44]) and follow-up (knowledge; attitudes; worry; decisional conflict, 16 items [37]) questionnaires, and the questionnaire for the historic study arm participants (knowledge; attitudes; worry; health literacy; decisional conflict) (Fig. 2).

**Fig. 2 Fig2:**
[figure not shown]
Schedule of enrolment, intervention, and assessments. Figure depicting the enrolment, intervention, and assessments according to SPIRIT 2013 statement [46]. ^§^ Assessed only in the historic cohort. BD background data, obtained from Statistics Denmark. Follow-up occurs throughout a period of 12 weeks. The final data will be obtained from the screening program IT system when all follow-up data have been collected. The complete data will then be merged with background data from Statistics Denmark

All questionnaires will be administered via REDCap Software (Version 6.12.0 - © 2016 Vanderbilt University) [45]. Data entry will occur automatically when the citizens complete the electronic questionnaires, hence no manual data entry will be required. The questionnaires are presented in Additional files 1, 2 and 3.

### Statistical methods

All statistical analyses will be carried out in Stata/SE 14 (STATACorp LP, College Station, TX, USA). Analyses will be carried out on a 5% significance level, stratified to gender. Estimates will be presented with 95% confidence intervals. Intention-to-treat analyses will be conducted.

Pearson’s chi-square test will be used to test differences in demographic characteristics between respondents and non-respondents as well as between those included in each study arm with lower educational attainment, in order to test for baseline differences. Furthermore, differences in educational attainment and screening uptake within 45 days in each study arm will be compared in order to evaluate the risk of attrition bias.

The main outcome of the trial is informed choice. Informed choice is difficult to measure and the evaluation will be based on adequate knowledge about CRC screening and consistency between attitudes towards CRC screening and screening uptake. This will be judged at group level not individual level. [46] Differences in distributions of responses to knowledge, attitudes, uptake, decisional conflict, and worries in the study arms will be analyzed using the independent sample t-test for continuous variables and Pearson’s chi-square test for categorical variables. The relative risk (RR) will be estimated for uptake using a logistic regression analysis with study arm 2 as the reference comparing to both study arm 1 and the historic cohort. Citizens are defined as having taken up CRC screening if they returned a stool sample within three months after the screening invitation was sent out [47]. For the numeric scale outcomes, a linear regression analysis will be conducted to compare the means between study arms 1 and 2 and study arm 2 and the historic cohort, using study arm 2 as the reference. For ordinal scales, not normally distributed as assessed by histograms and qq-plots, ordinal regression analyses will be conducted, estimating odds ratios for higher scores in study arm 1 and the historic cohort as compared to study arm 2, using study arm 2 as the reference.

Further, generalized linear models from the binary family will be conducted to test if socioeconomic variables (including health literacy) modify the effectiveness of the decision aid on knowledge, attitudes, and uptake. *P* values for these analyses will be estimated using the Wald test.

Few missing data are expected in registry and IT system data, since these systems are almost 100% complete [48]. Missing data may occur with the questionnaire data. In the scoring of health literacy, no more than three missing out of 16 items is accepted, otherwise the score cannot be calculated [41]. This is in contrast to the decisional conflict scale, in which the number of missing items is considered when calculating the final score [37]. In the knowledge scale, all questions are multiple choices and the response category “I don’t know” is represented in every item, giving the respondents a possibility to answer even if they are in doubt. The answer “I don’t know” and missing values are coded as wrong answers in the final scoring.

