### Outcomes

The outcomes assessed in this trial are presented in Table 1.

**Table 1 Tab1:** Trial outcomes

Outcome	Characteristics	Assessment time	Comparisons^a^	Null Hypothesis^a^
Primary outcome (Informed choice elements)				
Knowledge	Numeric scale	Baseline	1 vs. 2	No difference
	Numeric scale	Dif_Follow-up-baseline_^b^	1 vs. 2	1 > 2
	Numeric scale	Follow-up	1 vs. 2 vs H	1 > 2 and 1 > H
Attitudes	Numeric scale	Baseline	1 vs. 2	No difference
	Numeric scale	Dif_Follow-up-baseline_^b^	1 vs. 2	No difference
Uptake	Dichotomous	Follow-up	1 vs. 2 vs H	1 > 2 and 1 > H
Secondary outcomes				
Decisional conflict	Numeric scale	Follow-up	1 vs. 2 vs H	1 < 2 and 1 < H
Worry	Numeric scale	Baseline	1 vs. 2 vs H	No difference
	Numeric scale	Dif_Follow-up-Baseline_^b^	1 vs 2	1 < 2
Effect modifiers and confounders				
Health literacy	Numeric scale	Baseline	1 vs. 2 vs. H	No difference
Background data				
Family income	Categorical	Post survey	1 vs. 2 vs. H	No difference
Occupation	Categorical	Post survey	1 vs. 2 vs. H	No difference
Marital status	Dichotomous	Post survey	1 vs. 2 vs. H	No difference
Ethnicity	Categorical	Post survey	1 vs. 2 vs. H	No difference

*H* historic study arm

^a^Group 1 refers to the intervention group and group 2 refers to the control group

^b^Dif_Follow-up-Baseline_: The mean increase or decrease in knowledge, attitude, and worry-score from baseline to follow-up will be estimated. Means will be compared between the two study arms

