### Power calculations

The smallest difference between outcomes between groups is expected to be found in attitudes estimates (a 14% difference in proportions having a positive attitude towards screening [19]) Based on this assumption, power calculations (considering a 5% significance level and an 80% statistical power) indicate that we need to include 200 citizens with lower educational attainment in each group. We expect 47% of citizens invited to CRC screening not to return a stool sample within 45 days. Further, we know that 26% of the population has lower educational attainment [49]. By combining mailed invitations and reminders with telephone calls, we aim to reach a response rate of at least 60% for baseline questionnaire and 80% for follow-up (i.e. study participants). Further, we expect a 50% response rate in the historic study arm. In order to be able to make gender stratified analyses, and considering the rate of screening reminder, rate of lower educational attainment, and questionnaire response rate, we need to include 5000 citizens in each study arm.

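### Several co-primary elements are each tested at an unadjusted 5% by gender, no rule says which must succeed, and 5000 per arm does not give the stated 200 per gender

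*Protocol article*

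**What the plan says.** Table 1 of the protocol article groups knowledge, attitudes and uptake under "Primary outcome (Informed choice elements"), and the Primary outcome section confirms the plural: "Informed choice will be evaluated based on the following primary outcomes: consistency of knowledge about CRC screening, attitudes towards CRC screening, and screening uptake". For knowledge, that section adds: "Post-intervention levels and changes from baseline to follow-up will be evaluated".

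After the intervention, Table 1 has four primary contrasts of intervention (1) against control (2): knowledge change, knowledge at follow-up, attitude change and uptake. Follow-up knowledge and uptake are also compared with the historic cohort (H); knowledge change and attitude change are not. The column is labelled as null hypotheses, but entries such as 1 > 2 can only be expectations. For attitude change the entry is no difference.

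The Statistical methods section sets one error level for everything: "Analyses will be carried out on a 5% significance level, stratified to gender". It says that informed choice rests on sufficient knowledge together with agreement between attitude and uptake, and then: "This will be judged at group level not individual level". In the relative-risk analysis of uptake the historic cohort is compared with control, with "study arm 2 as the reference comparing to both study arm 1 and the historic cohort".

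The Power calculations section takes "a 14% difference in proportions having a positive attitude towards screening" as the smallest expected difference and reports that "power calculations (considering a 5% significance level and an 80% statistical power) indicate that we need to include 200 citizens". That number is per group and counts only the low-education target population. The section then gives 5000 per arm as the number that allows gender-stratified analyses after the expected losses.

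**The concern.** Two things are fixed badly.

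First, there are several primary contrasts, each at 5% and by gender, with no ordering, no adjustment and no statement of which results, or how many, would show that the decision aid works. A single significant result in one gender could then be reported as an effect on the primary outcome, and the 5% level would not apply to the trial's main conclusion.

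Second, gender-specific testing needs the 200 per group within each gender. If the planned sample does not deliver that, the protocol's own analysis is underpowered by its own standard, while the pooled comparison would have ample power.

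**Working it through.** **Inputs from the Power calculations section.** Alpha 5%, power 80%, a 14-point difference, 200 per group, 5000 sampled per arm, 60% baseline response, 80% follow-up response, 47% not returning a sample within 45 days, 26% with lower educational attainment.

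**Assumptions.** Two-sided tests (sidedness is not stated), equal numbers of men and women, and a range of base rates, since none is given.

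**1. Reproducing the 200.** With p1 = 0.43, p2 = 0.57 (the worst case, centred on 50%) and no continuity correction:

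n = [1.96·√(2·0.5·0.5) + 0.8416·√(0.43·0.57 + 0.57·0.43)]² / 0.14² = 199.04, rounded up to 200.

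The stated figure is reproduced. A one-sided test would give 157. Other base rates give fewer: 196 at 50 vs 64%, 176 at 60 vs 74%, 141 at 70 vs 84%.

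**2. What 5000 per arm yields.**

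- 0.60 × 0.80 × 0.47 × 0.26 = 0.058656
- 5000 × 0.058656 = 293 evaluable per arm
- 293 / 2 ≈ 147 per gender per arm
- One group of 200 needs 200 / 0.058656 = 3410 sampled; two gender strata of 200 need 400 / 0.058656 = 6820 sampled per arm.

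The stated 5000 corresponds to neither.

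**3. Power for a 14-point difference** (two-proportion normal approximation):

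| Base rates | 147 per gender, alpha 0.05 | 293 pooled, alpha 0.05 | 293 pooled, alpha 0.025 | 293 pooled, alpha 0.0167 |
|---|---|---|---|---|
| 43 vs 57% | 67% | 93% | 88% | 84% |
| 50 vs 64% | 68% | 93% | 88% | 85% |
| 60 vs 74% | 73% | 95% | 92% | 89% |
| 70 vs 84% | 82% | 98% | 96% | 95% |

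These figures are for a dichotomous outcome. Table 1 analyses knowledge and attitudes as numeric scales, so for those they are only a guide.

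**4. False-positive chance, intervention vs control, if any one significant result counts.** For k independent tests it is 1 − 0.95^k:

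- Four contrasts × two genders, k = 8: 1 − 0.95⁸ = 33.7%
- Without attitudes, k = 6: 1 − 0.95⁶ = 26.5%
- Four contrasts pooled over gender, k = 4: 1 − 0.95⁴ = 18.5%

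The tests are not independent. A simulation of 400,000 runs, with correlation 0.5–0.9 between the two knowledge measures and 0–0.5 between the other pairs (assumed values), men and women independent, gives 26–33% for the eight tests and 14–18% for the four pooled tests.

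**The case against.** The strongest reply is that the protocol does not say that any one result wins. It describes informed choice as a construct whose elements are read together; if all had to succeed jointly, there would be no inflation. This stands in part: the error rates above are conditional on the any-one reading. But the protocol does not state a joint rule either. One would be hard to apply, because Table 1 expects no difference in attitude change while the sample size is built on an attitude difference. For the same reason attitude is a doubtful route to a claimed success, so the six-test figure is given as well.

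It can also be said that gender stratification was planned for in the sample size. It was, but step 2 shows that the allowance falls short. Stratification might instead mean one combined stratified test, which leaves four tests and 14–18%. The wording does not settle this, although sizing the trial for gender strata points to separate analyses.

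A multiplicity rule could sit in an analysis plan that is not shown. The protocol, however, is not silent: it sets 5% for all analyses.

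A reader might infer more than the document supports:

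- **That a chance positive is likely.** Every count tried here stays below 50%. The highest, 46% for 12 independent tests (1 − 0.95¹²; 36–43% with correlation), includes intervention-versus-historic contrasts. The Study design section introduces that cohort to assess the effect of the questionnaire, not of the decision aid.
- **That power is halved.** The sample is halved. Power falls from 93% to 67% in the worst case and by less at other base rates.
- **That every primary outcome has two comparators.** Only follow-up knowledge and uptake do.

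**Conclusion.** The point holds in this form. The protocol names several primary elements, tests each at an unadjusted 5% by gender, and gives no usable rule for success. On the any-one reading, the randomised comparison carries roughly a one-in-four to one-in-three chance of at least one false positive, against a nominal 5%. This rests on that reading, on separate tests in men and women, and on the assumed correlations.

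Independently of that, the protocol's own rates give about 147 evaluable citizens per gender per arm where it requires 200. Per-gender power reaches 80% only when the base rates are near 70 vs 84%. This rests on an equal gender split and on the planned response rates being met.

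The comparison with the historic cohort is also inconsistent: Table 1 sets it against the intervention arm, the regressions in Statistical methods against control.

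**What to change.** 1. Make the primary analysis the randomised intervention-versus-control comparison pooled over gender, with gender as a covariate.
2. Name two superiority endpoints: knowledge at follow-up adjusted for baseline, and uptake. Apply Holm adjustment over the two and state what pattern of results counts as success. At the strictest step (alpha 0.05/2 = 0.025), pooled power for a 14-point difference in a proportion is about 88% or more.
3. Report baseline-adjusted attitude as an estimate with its confidence interval, which fits the expectation in Table 1. Bring it into the Holm family only if a direction is stated; the strictest step is then 0.05/3 = 0.0167, with pooled power about 84% or more.
4. Make gender-specific estimates secondary, with an arm-by-gender interaction test.
5. Correct the Power calculations section to say that 5000 per arm is expected to give about 147, not 200, per gender, and state the base rate used.
6. Label historic-cohort contrasts exploratory, and reconcile Table 1 with the Statistical methods section on the group against which the cohort is compared.

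The cost is wording only, with no further participants. The downside is a slightly stricter threshold for the first element rejected, and gender-specific results lose primary status.

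### Informed choice is defined by consistency between attitude and uptake but judged only from separate arm-level comparisons, which cannot measure that consistency

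*Protocol article*

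**What the plan says.** Statistical methods states: "The main outcome of the trial is informed choice". It calls informed choice hard to measure and says that "the evaluation will be based on adequate knowledge about CRC screening and consistency between attitudes towards CRC screening and screening uptake". The next sentence fixes the level of analysis: "This will be judged at group level not individual level".

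The Primary outcome section also uses the language of agreement, naming "consistency of knowledge about CRC screening, attitudes towards CRC screening, and screening uptake".

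The analyses that follow are separate: "Differences in distributions of responses to knowledge, attitudes, uptake, decisional conflict, and worries in the study arms will be analyzed". The methods are t-tests, chi-square tests, and logistic, linear or ordinal regression, each on one outcome. Table 1 groups the rows under the label "Primary outcome (Informed choice elements" and has rows for knowledge, attitudes and uptake. It has none for informed choice or for agreement between attitude and uptake. The effect-modification models involve socioeconomic variables and health literacy; they do not relate attitude to uptake.

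The Discussion says that the trial examines whether decisions not to be screened are informed.

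**The concern.** Consistency between what a citizen thinks of screening and what that citizen does is a property of the individual. A mean attitude score and a proportion screened in each arm describe two separate distributions and do not say whether the people with positive attitudes are the people who were screened. Combining knowledge with consistency needs a further joint distribution that is not analysed either.

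What is at stake is the headline conclusion. The trial could obtain the result that Table 1 appears to expect and still not know whether the decision aid raised or lowered the share of citizens making an informed choice. The statement about informed non-uptake has the same problem, because it needs the non-participants' own knowledge and attitudes.

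This is not a detail left to an analysis plan. The protocol positively rules out the individual level.

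**Working it through.** **1. The plan's own figure.** The only sample-size input in Power calculations is a 14-point difference in the proportion with a positive attitude (5% level, 80% power), giving 200 per group. No baseline rate is stated, so I assume one. For two proportions, two-sided, with pooled variance under the null:

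n = [1.960·√(2p̄(1−p̄)) + 0.842·√(p₁(1−p₁) + p₂(1−p₂))]² / (p₁−p₂)²

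- 43% vs 57%: (1.386 + 0.589)² / 0.0196 = 199.04, so 200.
- 50% vs 64%: 196.

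The 200 is reproduced for a baseline near 50%. It powers one element, not informed choice.

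**2. Agreement from arm-level proportions.** Let a = P(positive attitude), u = P(uptake) and J = P(positive attitude and uptake). Then

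agreement = J + (1 − a − u + J) = 1 − a − u + 2J,

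where J can lie anywhere from max(0, a+u−1) to min(a, u). The planned analyses estimate quantities related to a and u, but not J. The documents give no values for a and u in the analysed population, so the values below are assumptions:

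| a | u | range of J | range of agreement |
|---|---|---|---|
| 50% | 50% | 0–50% | 0–100% |
| 60% | 40% | 0–40% | 0–80% |
| 60% | 30% | 0–30% | 10–70% |

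**3. Adding knowledge.** With k = P(adequate knowledge), the informed share can run from max(0, k + lowest agreement − 1) to min(k, highest agreement). For k/a/u = 50%/60%/40% this is 0–50%; for 60%/60%/40% it is 0–60%. A 10-point rise in knowledge leaves the two ranges overlapping almost entirely.

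**4. Does comparing arms rescue it?** I read the directions in Table 1 as expected results: uptake higher in arm 1, no difference in attitude change. Assume a = 60% in both arms, and in arm 2 u = 40% and J = 30%:

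- Arm 2 agreement: 1 − 0.6 − 0.4 + 0.6 = 60%.
- Arm 1, uptake 50%, all 10 extra points among citizens with a positive attitude (J = 40%): 1 − 0.6 − 0.5 + 0.8 = 70%.
- Arm 1, uptake 50%, all 10 extra points among citizens with a negative attitude (J = 30%): 1 − 0.6 − 0.5 + 0.6 = 50%.

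The attitude and uptake proportions are identical in the two arm 1 scenarios. In one, consistency rises by 10 points; in the other it falls by 10.

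**5. Can the joint measure be built?** Yes. Knowledge and attitude are collected per citizen at follow-up (Questionnaires). Uptake is obtained per citizen from the screening database with consent (Study processes; Primary outcome). The follow-up questionnaire goes out 45 days after the reminder, about day 90, which is also the end of the uptake window.

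**The case against.** The strongest defence is that group-level judgement is an open and deliberate choice, with a citation, and that the declared primary outcomes are the elements themselves. The Primary outcome section uses the plural, Table 1 gives each element its own row and direction, and each comparison between randomised arms is usable whatever becomes of the composite. That stands: the planned tests are not invalid. What it does not rescue is the word consistency, or the claim about informed non-uptake, because disclosing the choice does not make the quantity estimable. The source cited for it cannot be checked here.

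Three stronger readings are tempting, and the documents do not support them.

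- A reader might infer an inflated false-positive rate, about 14% for three independent tests at 5% (1 − 0.95³). That needs a rule that any one positive element counts as success. The protocol states no such rule, and Table 1 points to a pattern in which an attitude difference would count against the expected result.
- A reader might take 0–80% as the likely size of error. It is a logical bound for one arm under assumed rates; the 0% end requires that no citizen with a positive attitude is screened and every other citizen is.
- A reader might conclude that the registered primary outcome must be replaced by one composite test. The documents give no expected proportion of informed choices on which to power it, and no cut-offs for it.

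An individual-level measure also has a weakness of its own. Follow-up attitude is recorded around or after the end of the uptake window and may have adjusted to what the citizen already did, which would raise apparent consistency.

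**Conclusion.** The point holds and should be fixed. As written, the plan cannot estimate the consistency that defines its main outcome, and its expected result is compatible with informed choice rising or falling. The non-identifiability is a matter of logic and depends on no assumed rate; only the illustrated ranges (0–80% at 60%/40%, 0–100% at 50%/50%) do. The practical size of the problem in this trial cannot be stated from the documents. The defect lies in the match between outcome definition and analysis, and hence in what may be concluded; the comparisons of knowledge, attitudes and uptake keep their value.

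**What to change.** Replace the sentence restricting judgement to group level with a prespecified individual-level measure, reported alongside the planned element analyses:

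- A citizen has made an informed choice if follow-up knowledge is adequate (cut-off on the seven items fixed before the data are seen) AND follow-up attitude matches the citizen's own 90-day uptake: positive with uptake, or negative without.
- Fix the attitude cut-off on the 4–28 scale in advance, with a rule for scores at the midpoint, (4 + 28)/2 = 16.
- Compare the proportion between arms 1 and 2 with a 95% confidence interval.
- Add sensitivity analyses using baseline attitude and alternative cut-offs for knowledge and attitude.

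If this is not added, limit conclusions to the three elements and drop statements about consistency or about whether non-uptake was informed.

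The cost is revised protocol and analysis-plan wording and one derived variable; no new data are needed. Dichotomising loses information, the result will depend on the cut-offs, and no power can be stated because no expected proportion of informed choices is given. As a guide to precision only, at 200 per group the 95% interval for a difference is at its widest about ±1.96·√(2 × 0.25/200) = ±9.8 points.

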#### Study processes

Seven to 20 weeks before the invitation date, the included citizens in study arms 1 and 2 will receive a link to the baseline questionnaire via their digital mail (with remote printing for exempted citizens). Questionnaire reminders will be sent out after two weeks. Instead of a second questionnaire reminder, non-respondents will be contacted via telephone after four weeks and invited to fill out the questionnaire via telephone interview. In a pilot study, the response rates among lower educational attainment and medium/higher educational attainment citizens using an invitation and a two-week reminder were assessed at 27% and 55%, respectively. The response rates increased to 40% and 64%, respectively, in the two groups, by using telephone interviews. Accordingly, we expect telephone interviews to help reach more of the lower educational attainment citizens. Questionnaire respondents will also be asked for consent to the obtaining and analysis of screening data (date of invitation, reminder, receipt of test in laboratory, and test result) from the screening program database.

Citizens who respond to the questionnaire and give consent to the use of registry data will be randomly allocated into study arms 1 and 2. Allocation will be performed in the ratio 1:1 and will use a computer-generated algorithm for randomization, based on a simple randomization procedure. Randomization will be conducted based on the study participants’ record-ID numbers. Participants will not be able to change study arm after allocation and there will be no blinding.

Citizens who take up screening within 45 days after the screening invitation and citizens with medium or higher educational attainment (i.e. 10 years or more of education) will be excluded from the analyses after randomization. This might cause attrition bias. However, randomization will be conducted externally before screening uptake is known. Furthermore, educational attainment will not be available to researchers at an individual level, unless data are pseudonymized. However, educational level and screening uptake within 45 days of invitation is not expected to be associated with study arm and, hence, no attrition bias is expected.

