## Abbreviations

CRC: Colorectal cancer
FIT: Fecal immunochemical test
gFOBT: Guaiac fecal occult blood test
IPDASi: International patient decision aid standards collaboration instrument
LEAD trial: Lower educational attainment decision aid trial
RR: Relative risk

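### The plan names a relative risk for uptake but specifies logistic regression, which directly yields an odds ratio, and states no conversion

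*Protocol article*

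**What the plan says.** The Statistical methods section states: "The relative risk (RR) will be estimated for uptake using a logistic regression analysis with study arm 2 as the reference". The sentence goes on to apply this both to study arm 1 and to the historic cohort. The Abbreviations list confirms the intended measure: "RR: Relative risk".

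Uptake is binary. Under Primary outcome, citizens count as having taken up screening "if they return a stool sample within three months (90 days) after the screening invitation has been sent out". It is one of the three elements on which informed choice is judged: "consistency of knowledge about CRC screening, attitudes towards CRC screening, and screening uptake".

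Two other sentences in Statistical methods bear on the point. For scales that are not normally distributed, "ordinal regression analyses will be conducted, estimating odds ratios for higher scores" is planned, so the text uses odds ratio and relative risk as separate terms. For effect modification, "generalized linear models from the binary family will be conducted to test if socioeconomic variables" modify the effect of the decision aid. That model class can deliver a relative risk, but no link is named and it is not assigned to the main uptake estimate.

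**The concern.** The measure and the model in the uptake sentence do not match. Logistic regression works on log odds, so the coefficient for study arm, once exponentiated, is an odds ratio. An analyst following the text must either add a step that is not described or report a quantity other than the one promised.

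Readers will take a figure labelled RR as a ratio of participation proportions. If it is really an odds ratio, it overstates the proportional change in participation, and a screening programme using it would expect more extra participants than the data support. The same holds for the comparison with the historic cohort, which the sentence also covers.

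**Working it through.** **Inputs.** The measure (RR), the model (logistic) and the reference group (arm 2) come from Statistical methods. The protocol gives no numerical RR or odds ratio for uptake, so there is no figure of its own to reproduce. The 200 per group under Power calculations rests on attitudes and does not enter here.

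Uptake in control arm 2 within the analysed group, p0, is not stated. Study processes says that "Citizens who take up screening within 45 days after the screening invitation and citizens with medium or higher educational attainment" are excluded from the analyses after randomization. The outcome compared between arms 1 and 2 is therefore return by day 90 among citizens who had not returned a sample by day 45. I treat p0 as an assumption and show a range.

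**Formulas.** With uptake p1 in arm 1:

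- RR = p1/p0
- OR = [p1/(1 − p1)] / [p0/(1 − p0)]
- It follows that (OR − 1)/(RR − 1) = 1/(1 − p1), so the gap grows with uptake in arm 1.

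**True RR of 1.20, p0 assumed:**

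| p0 | p1 | OR | Excess of OR − 1 over RR − 1 |
|---|---|---|---|
| 5% | 6% | 1.21 | 6% |
| 10% | 12% | 1.23 | 14% |
| 20% | 24% | 1.26 | 32% |
| 30% | 36% | 1.31 | 56% |
| 50% | 60% | 1.50 | 150% |

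For example, at p0 = 30%: (0.36/0.64)/(0.30/0.70) = 0.5625/0.4286 = 1.31, and 1/(1 − 0.36) = 1.56.

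**Effect on the interval, and whether the logistic model can be kept.** The protocol's planning rates give 5000 × 0.60 × 0.47 × 0.26 × 0.80 = 293 analysed citizens per arm. I built one data set with assumed uptake of 30% against 42%, that is, 88/293 against 123/293.

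- Logistic, exponentiated coefficient: (123 × 205)/(88 × 170) = 1.69, 95% CI 1.20 to 2.37.
- Log-link binomial model: RR = 123/88 = 1.40, 95% CI 1.12 to 1.74.
- Ratio of predicted risks from the same logistic fit: 0.420/0.300 = 1.40.

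Both confidence limits move away from 1 when the odds ratio is read as an RR. The third line shows that the logistic model itself is not the obstacle; the missing step is.

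**The case against.** The strongest reply has three parts.

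**The protocol promises an RR, and a logistic model can supply one.** Standardising predicted risks returned 1.40 in the example, the same as the log-link model. Nothing in the text says that the exponentiated coefficient will be labelled RR, and such detail is often left to a fuller plan. This stands in part: the overstatement is conditional. But the article does not merely omit a detail. It pairs a measure with a model that does not directly give it, in a section that uses the term odds ratio elsewhere.

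**The gap may be small.** A reader might infer that uptake is common, and the distortion therefore large, from the Power calculations: "We expect 47% of citizens invited to CRC screening not to return a stool sample within 45 days", which implies 53% returning by then. The document does not support that inference for arms 1 and 2, because those 53% are the citizens removed from the analysis. Uptake among those who remain is not given; at 5% or 10% the gap is minor. A reader might instead argue that uptake cannot be low because the Power calculations call the 14% difference in attitudes the smallest expected between groups. Taken literally, that would put uptake in arm 1 at 14% or more. But the figure concerns attitudes, and the protocol gives no expected uptake difference, so I do not rely on it.

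**The test is untouched.** Pearson's chi-square test is planned for categorical outcomes and does not depend on the choice between RR and odds ratio. This stands in full. Randomization, data collection and sample size are also unaffected.

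**Conclusion.** The mismatch is real: the text names a relative risk, specifies a model whose direct output is an odds ratio, and gives no conversion. It concerns the size and reading of an estimate on a primary element, not the validity of the trial or the test of no effect.

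The plan cannot be said to overstate the effect as it stands. Overstatement follows only if the exponentiated logistic coefficient is reported as the RR. Its amount rests on an unstated rate: for a true RR of 1.20, the reported value would range from 1.21 at an assumed control uptake of 5% to 1.50 at 50%. The expected 47% non-return by day 45 should not be used as evidence that uptake is common in the analysed group. No separate size can be given for the historic cohort comparison, because no uptake rate is stated for it.

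**What to change.** Replace the uptake sentence in Statistical methods with one that names a model delivering the promised measure, with arm 2 as reference for both comparisons. Either of these serves:

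- a binomial generalized linear model with log link, with Poisson regression and robust standard errors as the fallback if it does not converge; or
- the logistic model as planned, with the RR and its confidence interval obtained from standardised predicted risks.

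If neither is wanted, keep the logistic model and label the estimate an odds ratio throughout.

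The cost is one sentence in the plan and one changed or added Stata command. Design, data collection and sample size do not change, and the correction can be made at any time before the analysis.
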